# Trial to assess the tolerability of using felodipine to upregulate autophagy as a treatment of Huntington’s disease (FELL-HD): a phase II, single-centre, open-label, dose-finding trial protocol

**DOI:** 10.1136/bmjopen-2024-087983

**Published:** 2024-08-21

**Keywords:** clinical trial, neurology, clinical trials

## Abstract

**Introduction:**

Huntington’s disease (HD) is an autosomal dominant neurodegenerative disorder that presents with a progressive movement disorder along with cognitive and psychiatric problems. It is caused by a Cytosine-adenin-guanine (CAG) expansion in exon 1 of the huntingtin gene which codes for mutant huntingtin (mHTT) that over time accumulates in cells, causing dysfunction and then death through new toxic gain-of-function mechanisms. Autophagy has been shown to be critical for the degradation of diverse intracytoplasmic aggregate-prone proteins that cause neurodegenerative disease, including mHTT. From a screen of a library enriched in approved drugs, felodipine was selected as the most suitable candidate showing strong autophagy-inducing effects in preclinical models of HD. We are, therefore, conducting a trial to assess the safety and tolerability of felodipine in people with early HD.

**Methods and analysis:**

FELL-HD is a phase II, single-centre, open-label, dose-finding trial in people with early HD. 18 participants with early clinical features of the disease will be treated with felodipine for 58 weeks, with a further 4-week follow-up. The primary outcome measure is the number of adverse events attributable to felodipine. Exploratory outcomes include additional measures of motor and cognitive function, non-motor symptoms and quality of life scales, as well as peripheral and central disease biomarkers assessed through brain MRI. Analysis of blood and cerebrospinal fluid will also be performed through an associated sample study, FELL HD-s.

**Ethics and dissemination:**

The study was approved by the London-Brent Research Ethics Committee (reference 22/LO/0387) and has been accepted by the Medicines and Healthcare products Regulatory Agency for clinical trials authorisation (reference CTA 12854/0256/001-0001). A lay summary of the results of the trial will be uploaded to our research group website which is publicly accessible. A webinar or in-person open day, to present results of the trial to participants and our wider cohort of patients who attend our centre, will be held once the trial is completed. The results of the trial will also be published in scientific journals and presented at national and international conferences.

**Trial registration numbers:**

EudraCT-2021-000897-27, ISRCTN56240656.

STRENGTHS AND LIMITATIONS OF THIS STUDYA comprehensive approach to investigate whether a drug repurposed to slow disease progression works through upregulating autophagy is feasible and well tolerated in patients with a progressive neurodegenerative disorder.The duration of treatment to study this with exploratory measures around efficacy which is possible given the trial is a yearlong.The open-label nature of the study may mean participants are biased to the effects of the medication and the small number of participants treated.We are unable to directly measure target engagement around autophagy as we have no biological measures to look at this process in the brain.

## Introduction

 Huntington’s disease (HD) is a progressive, genetic, neurodegenerative disorder that affects approximately 5700 people in the UK,^1^ with 5 times as many at risk of having inherited the gene. Clinical features typically emerge at the height of normal adult working life, namely between 30 and 50 years and include motor dysfunction, neuropsychiatric disturbances and cognitive difficulties. The disease runs a progressive course over about 20 years to death. There are currently only limited symptomatic therapies for HD, and these largely target only the motor features, there is, therefore, an urgent need for disease-modifying agents for people with HD.

The major pathological problem in HD relates to the production of abnormal huntingtin, called mutant huntingtin (mHTT), which over time aggregates and causes neuronal cells to dysfunction and then die. This production occurs as a result of inheriting the abnormal HD gene. Like many intracytoplasmic, aggregate-prone, mutant proteins linked to neurodegenerative diseases, the mHTT causes pathology via new toxic gain-of-function mechanisms. Given all this, it is clear that the logical way to try and stop HD is either to prevent the mHTT being formed (which is being investigated in trials using, eg, antisense oligonucleotides^2^) or clear it more efficiently from the cell.

One normal intracellular pathway that clears this and many abnormal proteins is called autophagy, which is initiated by double-membraned structures, called autophagosomes, that engulf portions of cytoplasm. Autophagosomes then end up fusing with lysosomes, where their contents are degraded.^3^ Autophagy has been shown to be critical for the degradation of diverse intracytoplasmic aggregate-prone proteins that cause neurodegenerative disease, including mHTT, as well as other proteins linked to neurodegenerative disorders of the brain^4^,^7^ and autophagy-upregulating drugs have been shown to enhance the clearance of these proteins, thereby attenuating their toxicities in Drosophila, zebrafish and mice (reviewed in Menzies *et al*^3^). This concept that autophagy upregulation may have therapeutic value in diverse diseases caused by aggregate-prone intracytoplasmic proteins has been subsequently validated by many groups and is now a major therapeutic target in neurodegeneration.

In preclinical studies, using a screen of a library enriched in approved drugs that induce autophagy, verapamil, an L-type calcium channel blocker, was identified as an inducer of autophagosome formation. Verapamil also reduced the percentage of cells with aggregates of mHTT in autophagy competent but not in autophagy-null cells.^8^ L-type calcium channel blockers are antihypertensive drugs and are widely used in the population so this family of drugs was considered to be suitable for repurposing for long-term treatment. As it was found verapamil does not cross the blood–brain barrier, this would make it unsuitable for the chronic treatment of primary central nervous disorders. A panel of currently prescribed L-type calcium channel blockers was screened to identify a blood–brain barrier-penetrant member that showed strong autophagy-inducing effects as well as having a long half-life in humans.^9^ Felodipine was selected as the most suitable candidate for further assessments. Felodipine has been found to induce autophagy in neurons in vitro and ameliorate in vivo toxicities in relevant animal models.^9^ Pharmacokinetic studies have also been performed in mice to determine the optimal treatment regime, which would mimic the plasma concentration that the drug reaches in humans at currently prescribed doses of 10 mg/day (the standard dose used for treating hypertension). Subcutaneous minipumps were used in mice with a protocol that mimicked the plasma concentrations of the drug seen in humans taking felodipine, and good brain penetrance of the drug was found with some behavioural benefits.^9^ However, to truly verify this, longer studies would be needed but these could not be performed because of Home Office restrictions on the long-term use of osmotic minipumps in mice.

Further support for this approach comes from epidemiological studies, which suggest that the use of felodipine may reduce the incidence of another disease associated with protein aggregation, Parkinson’s disease, in hypertensive patients.^10^ Additionally, the safety profile of felodipine is already established and is licensed to treat hypertension. The average half-life of felodipine in the terminal phase is 25 hours, and steady state is reached after 5 days. There is no significant accumulation during long-term treatment and the medication only needs to be administered once a day. All of this, in combination with the preclinical work, supported the decision to test felodipine in people with early HD into a clinical trial.

## Methods and analysis

### Overview

FELL-HD is a phase II, open-label trial in people with early HD that aims to test the safety and tolerability of different doses of felodipine. The trial will investigate whether three different doses of felodipine are tolerated over a 58-week treatment period, followed by a 4-week washout follow-up period.

18 participants will be recruited and allocated to one of three cohorts in alternating fashion that will all receive felodipine. All participants will begin on 2.5 mg of felodipine with the dose being increased every 2 weeks from baseline to the cohort maximum dose, only if the previous dose has been tolerated. Cohort 1 will receive a maximum of 5 mg, cohort 2 will receive a maximum of 10 mg and cohort 3 will receive a maximum of 20 mg. The dosing schedule is summarised in table 1. Safety assessments will be performed every 2 weeks up to week 8 while participants reach their maximum allocated dose. Following this, clinical and safety assessments will be performed every 8 weeks until week 40. At week 48, a telephone visit will be performed and participants will then be seen at week 57 for safety and clinical assessments. A repeat telephone visit will be performed at week 58 which is when participants will end their treatment phase with felodipine. Clinical and safety assessments will then be performed at week 62 for the final trial visit. For the schedule of visits, refer to figure 1.

**Figure 1 F1:**
[figure not shown]
Flow chart. CSF, cerebrospinal fluid; IMP, Investigational medicinal product

**Table 1 T1:** Dosing schedule for all cohorts

Time point	Felodipine dose (mg)		
	Cohort 1	Cohort 2	Cohort 3
Week 0	2.5	2.5	2.5
Week 1	2.5	2.5	2.5
Week 2	5	5	5
Week 3	5	5	5
Week 4	5	10	10
Week 5	5	10	10
Week 6–57	5	10	20
Week 58	Stop	Stop	Stop

All participants involved in the FELL-HD trial will also be asked if they would like to participate in an associated sample study called FELL-HD-s (Full title: A trial to assess markers of autophagy in patients with Huntington’s disease who have been treated with felodipine, IRAS 297596). The FELL-HD-s study involves research blood samples being taken at the participants’ FELL-HD trial visits, as well as an optional component to collect cerebrospinal fluid (CSF) at baseline and week 57. The CSF collection is optional to ensure that this inclusion does not impact recruitment.

While the primary objective of the FELL-HD trial is safety, we will also look at changes in clinical measurements of HD using validated motor and cognitive assessments between baseline and week 62. Changes in volumetric measures on MRI will also be evaluated as an exploratory measure if participants consent to this, as having an MRI is an optional component of the trial. In addition, our FELL-HD-s study will assess markers of target engagement of felodipine in blood and CSF samples.

### Patient and public involvement

People with HD who attend our National Health Service (NHS) HD clinic at the John Van Geest Centre for Brain Repair (VGB), University of Cambridge, gave input into the trial design. A patient and public involvement (PPI) panel of four patients who have been/are actively involved in other research projects through the clinic, provided feedback on the trial design and the commitment required by the participants. The PPI panel also reviewed our participant information sheets for clarity to ensure they were detailed enough and easy to understand, and a member of the panel attended the ethical committee meeting.

### Participant identification

Participants will be recruited from a single site in Cambridge, UK. Potential participants will be identified via the NHS HD clinic and from the database of people who have previously attended the NHS HD clinic. These will only be people who have indicated they are interested in being contacted about involvement in future research. The database holds detailed information about demographics, HD status and clinical assessments, comorbidities and medication that will assist in identifying potential participants that fit the inclusion/exclusion criteria as outlined in figure 2.

**Figure 2 F2:**
[figure not shown]
Inclusion/exclusion criteria. ACE-III, Addenbrookes Cognitive Examination III; HD, Huntington’s disease; MMSE, Mini Mental State Examination.

Alternatively, participants may be asked if they would be interested in the trial at their routine NHS HD clinic appointment.

All interested participants will be provided with a participant information sheet and after approximately 2 weeks (to give them sufficient time to consider the invitation), the trial team will contact them by telephone to see if they would like to participate. If the potential participant is interested, they will be invited to a screening visit where the participant’s understanding of the trial is confirmed and written informed consent is obtained before confirming eligibility through screening assessments. Informed consent will be taken by the principal investigator (PI) or subinvestigator (SI). However, if a potential participant is not interested, they will continue with their standard clinical care.

### Eligibility criteria

A potential participant will be considered eligible for recruitment to the FELL-HD trial if they meet the inclusion/exclusion criteria listed in figure 2. At the screening visit, a review of the participant’s medical history, demographics, vital signs, physical examination, safety blood sampling and clinical assessments will be used to determine eligibility.

Any participants who are deemed eligible to participate in the FELL-HD trial will be assessed for eligibility to take part in the sample study FELL-HD-s if they consent to this. Participants who consent to FELL-HD-s will be screened for HIV, hepatitis B virus (HBV) or hepatitis C virus (HCV) to determine eligibility.

### Outcome measures

The primary outcome measure for the FELL-HD trial is the number of adverse events (AEs) attributable to felodipine. An AE is any untoward medical occurrence in a participant that may or may not have a causal relationship to the treatment. Recording of AEs starts from the point of informed consent at the screening visit regardless of whether a participant has started the treatment or not.

Exploratory outcome measures of the trial include:

Changes in clinical measurements of HD using validated motor and cognitive assessment tools between baseline visit (week 0) and end of the trial (week 62).Change on a range of MRI volumetric measures between baseline (week 0) and end of the trial (week 62).

In the sample-study FELL-HD-s, the primary outcome measure is the change in mHTT levels in the blood between baseline (week 0) and end of the trial (week 62). The secondary outcome measurement is the change in neurofilament light chain (NFL) levels in the blood between baseline (week 0) and end of the trial (week 62).

Exploratory outcome measures of the FELL-HD-s-study include:

Change in level of felodipine in the blood between baseline and week 62.Change in level of felodipine in the CSF between baseline and week 57.Change in mHTT levels in the CSF between baseline and week 57.Change in NfL levels in the CSF between baseline and week 57.Change in level of glial fibrillar acidic protein (GFAP) in the blood between baseline and week 62.Change in level of GFAP in CSF between baseline and week 57.

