### Treatment allocation and dosing

Participants will be assigned to one of three dosing cohorts. Cohort 1 will receive a total of 5 mg daily, cohort 2 will receive a total of 10 mg daily and cohort 3 will receive a total of 20 mg daily. There will be six participants assigned to each cohort in an alternating fashion, that is, participant 1 will be allocated to cohort 1, participant 2 will be allocated to cohort 2, participant 3 will be allocated to cohort 3, participant 4 will be allocated to cohort 1 and so on. This will be performed by the trial coordinator.

All participants will start on 2.5 mg from baseline (week 0), if tolerated, all participants will have their dose increased to 5 mg at week 2 and cohort 1 will then remain on 5 mg until week 58. Those assigned to cohort 2 will have their dose, if tolerated, increased again to 10 mg at week 4 and will remain on 10 mg until week 58. Those assigned to cohort 3 will also have their dose increased to 10 mg at week 4 and then have their dose, if tolerated, increased for a third time to 20 mg at week 6 and will remain on 20 mg until week 58. Please refer to the dosing schedule in table 1.

The dose will only be increased where the previous dose has been tolerated, all judgements of intolerance will be at the PI discretion. Intolerance may be defined by an occurrence of an AE of moderate severity, which is either definitely or probably related to the felodipine. If a participant is unable to tolerate a dose, they will be moved back to the last dose they were able to tolerate within their cohort dosing. If the participant is already at the lowest dose then felodipine will be withdrawn. No dose rechallenge will be undertaken if a dose is reduced during the course of the trial.

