### Statistical methods

A statistical analysis plan (SAP) will be finalised and approved before the commencement of the analysis. The analysis will be performed on the modified intention-to-treat population, which includes all eligible participants who had at least one dose of investigational treatment and were not replaced during the trial. Participant data will be analysed according to their allocated cohort. The primary outcome is felodipine-related AEs, therefore, missing data are not expected. In all analyses, no imputation will be performed.

Participant data will be summarised by cohort. For the primary endpoint, no formal hypothesis testing will be performed. The statistical analysis will be mostly descriptive, with the number of felodipine-related AEs summarised by dosage for each cohort. All the exploratory endpoints described in the outcome measurement section will be summarised, and a significance test will be performed between baseline and week 57/62, using a paired t-test as the primary analysis and a Wilcoxon signed-rank test as the sensitivity analysis. No formal subgroup analysis will be performed. This trial has no predetermined ending criteria or formal interim analysis.

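### The primary outcome totals felodipine-related events of any severity, so on its own it cannot show how many of the six people in a cohort tolerated their dose

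*Protocol article*

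**What the plan says.** Outcome measures defines the primary outcome: "The primary outcome measure for the FELL-HD trial is the number of adverse events (AEs) attributable to felodipine". It sets no severity limit: "An AE is any untoward medical occurrence in a participant that may or may not have a causal relationship to the treatment". The only filter is attribution to felodipine.

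Statistical methods uses the same unit: "The statistical analysis will be mostly descriptive, with the number of felodipine-related AEs", broken down by dosage within cohort. It adds: "For the primary endpoint, no formal hypothesis testing will be performed". The abstract also gives the primary outcome as a number of events.

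On size, Treatment allocation and dosing states: "There will be six participants assigned to each cohort in an alternating fashion". The Overview gives the trial's question as whether three doses are tolerated over 58 weeks.

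A person-level idea with a severity grade appears once, in the dosing rule under Treatment allocation and dosing: "Intolerance may be defined by an occurrence of an AE of moderate severity", where the event is definitely or probably related to felodipine, and the judgement is left to the principal investigator. That rule governs dose steps. It is not named as an outcome. No outcome in the article is a number or proportion of participants affected.

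**The concern.** Tolerating a dose is a property of a person, and a total of events is not. Over 58 weeks one participant can report the same mild symptom many times, and each report counts as much as a serious event in someone else. With six people in a cohort, one frequent reporter can make up most of the total.

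A dose with many mild events in one person could therefore look worse than a dose with fewer but more severe events spread over several people. Sample size calculation says the data from this trial will inform the design of a phase 3 trial, so a misreading of tolerability by dose would carry forward.

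This is separate from differences in time on drug. It remains when every participant has the same weeks of exposure.

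**Working it through.** **Inputs from the article.** 18 participants in three cohorts; 3 × 6 = 18, and 1-2-3 alternation of 18 people gives 6/6/6, so the stated size reproduces. The primary unit is the event, with no severity threshold. The article gives no AE rate and no interval.

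**Step 1: the same total from opposite patterns (no assumed rate needed).** Take a cohort total of 12.

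- Two events in each of six people: 6/6 affected. Clopper-Pearson lower limit 0.025^(1/6) = 0.541, so 54–100%.
- Twelve events in one person: 1/6 affected. Lower limit 1 − 0.975^(1/6) = 0.004; upper limit is the 97.5% quantile of Beta(2, 5) = 0.641, so 0.4–64%.

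The planned summary is 12 in both cases.

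**Step 2: how often one person dominates (assumed rates).** Assumptions, not from the documents: a mean of 1, 2 or 4 related AEs per person, either independent (Poisson) or clustered (gamma-Poisson with shape 2, 1 or 0.5; a smaller shape means stronger clustering). Let Y be one person's count and S the sum of the other five. Among cohorts with at least one event, the chance that some person supplies half or more is

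[6 Σ P(Y=j) P(S≤j) − 15 Σ P(Y=j)² P(Y=0)⁴] / [1 − P(Y=0)⁶], with sums over j ≥ 1.

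The second term removes double counting when two people share all the events equally.

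| Mean per person | Independent | Shape 2 | Shape 1 | Shape 0.5 |
|---|---|---|---|---|
| 1 | 33% | 51% | 63% | 77% |
| 2 | 6% | 27% | 44% | 65% |
| 4 | 0.2% | 13% | 32% | 57% |

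The range is 0.2–33% under independence and 13–77% under clustering. A simulation of 200,000 cohorts per cell agrees.

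**Step 3: what an interval on the total would do.** The article plans none. If someone added the exact Poisson interval, a total of 12 would give 6.2–21.0 events for both patterns in Step 1. Simulated coverage of that nominal 95% interval for a six-person total is about 96% under independence. With clustering at shape 2, 1 and 0.5 it falls to 91, 87 and 78% (mean 1), 85, 77 and 64% (mean 2) and 77, 64 and 50% (mean 4).

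**Step 4: what participant-level reporting would show.** Exact 95% limits for six people: 0/6 gives 0–46%, 1/6 gives 0.4–64%, 3/6 gives 12–88%. For all 18: 0/18 gives 0–18.5%, 3/18 gives 4–41%.

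**Step 5: a limit of the participant count.** With independent events, the chance that all six have at least one related AE is (1 − e^−mean)^6: 0.865^6 = 42% at mean 2 and 0.982^6 = 90% at mean 4. The any-AE count can therefore reach its ceiling and stop separating doses.

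**The case against.** The plan is descriptive and puts no interval, test or dose comparison on the event total. A reader might infer that the primary result has no valid uncertainty. The documents do not support that, since it criticises an analysis nobody has planned. What stands is a caution: a Poisson interval, if added, would be too narrow when events cluster within people.

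A reader might also infer that switching to participants cures unstable comparisons between cohorts, because two equally safe doses can easily show a twofold difference in event totals. It does not. With an assumed true participant-level risk of 10–30%, two identical six-person cohorts differ at least twofold in 58–67% of cases, counting one against none. Most of that instability comes from the cohort size. The wide exact limits in Step 4 are likewise facts about six people and do not show that counting events is wrong.

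The SAP is not shown and may well tabulate participants affected and severity, so the absence of such tables cannot be assumed. Repeated events in one person are also a real burden, so event totals have a place.

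These objections narrow the point without removing it. The article itself fixes the primary outcome as an event count, and supporting tables in a SAP would not change which number leads.

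**Conclusion.** The point holds as a mismatch between the trial's question and its primary summary. Nothing stated is numerically wrong, and no error rate is at stake. The event total alone cannot distinguish 6/6 affected from 1/6 affected, and it gives mild recurrent events the same weight as serious ones.

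The 12-event example rests on no assumed rate. The dominance figures depend on assumed means and clustering. They are very small only where events are both frequent and independent (0.2% at mean 4). This is a worthwhile, inexpensive improvement to the primary summary and not a flaw that invalidates the trial.

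**What to change.** In Outcome measures and Statistical methods, make the headline primary summary the number and percentage of participants with:

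- at least one felodipine-related AE; and
- at least one felodipine-related AE of moderate or worse severity, using the grade already named under Treatment allocation and dosing.

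Give both per cohort and pooled, each with an exact Clopper-Pearson 95% interval. Keep event totals by severity alongside, with the number of participants contributing to each total. If any interval is put on a total, it should allow for clustering within people. With only six people such methods are also rough: a participant-level t interval covered 83–92% in the clustered scenarios above.

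The cost is wording and table shells, with no new visits, data or participants and no change to the dosing rule. There are two downsides. The any-AE count may saturate when events are common, which is why the moderate-or-worse count and the event totals stay. The intervals at six per cohort will be visibly wide.

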#### Biosample collection and processing

As part of the FELL-HD trial, full blood count, liver function tests and urea and electrolytes samples will be taken at every clinic visit and analysed at the Laboratory Research Services in Addenbrooke’s Hospital.

If participants also consent to the FELL-HD-s substudy, 7.5 mL of blood will be collected and tested for HIV, HBV and HCV status to confirm eligibility. Starting at the baseline (week 0) visit and every 8 weeks up to week 40 and then at week 57 and week 62, up to 75 mL of blood will be collected for analysis of markers of disease, as well as levels of felodipine in the blood.

Samples will be taken in two different types of blood collection tubes depending on which laboratories the specimens will be sent to. Two samples will be taken in 8 mL sodium heparin cell preparation tubes and centrifuged at centrifugal force (RCF) 1500×g for 30 min at room temperature for extraction of plasma. Three samples will be taken in 6 mL K2E blood collection tubes and centrifuged at RCF 1300×g for 10 min at 4°C for extraction of plasma.

If consented, CSF will be collected via lumbar puncture at baseline (week 0) before treatment commences and week 57, 1 week prior to the end of treatment. The CSF will be used to assess levels of felodipine, NfL, mHTT and GFAP. CSF will be centrifuged at RCF 400×g for 10 min at 4°C. After spinning, the CSF supernatant will be separated from the CSF cells and stored.

All aliquots for blood and CSF will be stored at −80°C until the end of the trial where they will then be sent to the analysing laboratory which will look at the above protein levels.

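### The FELL-HD-s blood felodipine outcome is read at week 62, about 27 half-lives after the last dose, so it cannot show exposure; the blood marker outcomes share this off-drug time point, although the CSF outcomes do not

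*Protocol article*

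**What the plan says.** All places are in the protocol article.

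- **Outcome measures** gives, among the exploratory outcomes of the sample study, "Change in level of felodipine in the blood between baseline and week 62". For the sample study as a whole, "the primary outcome measure is the change in mHTT levels in the blood between baseline (week 0) and end of the trial (week 62". Blood NfL (secondary) and blood GFAP (exploratory) are also changes from baseline to week 62. The four CSF outcomes (felodipine, mHTT, NfL, GFAP) are all changes from baseline to week 57.
- **Overview** ends dosing before that visit: "A repeat telephone visit will be performed at week 58 which is when participants will end their treatment phase with felodipine". The treatment period is "followed by a 4-week washout follow-up period". Table 1 agrees, with the cohort dose through week 57 and a stop at week 58.
- **Treatment allocation and dosing** fixes the start: "All participants will start on 2.5 mg from baseline (week 0".
- **Introduction** gives the pharmacokinetics: "The average half-life of felodipine in the terminal phase is 25 hours, and steady state is reached after 5 days". It adds: "There is no significant accumulation during long-term treatment".
- **Biosample collection and processing** schedules the research blood draws, for disease markers and felodipine levels: "Starting at the baseline (week 0) visit and every 8 weeks up to week 40 and then at week 57 and week 62". It places the second lumbar puncture one week before treatment ends.
- **Overview** (text after Table 1) says that FELL-HD-s is to assess target engagement in both blood and CSF.
- **Statistical methods** tests the exploratory endpoints from baseline to week 57 or week 62, without saying which endpoint takes which week.

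**The concern.** A change in drug concentration is informative only if at least one of the two samples is taken while the drug is present. Here one sample is at the start of treatment and the other is four weeks after it ends. In a trial built around three dose levels, the blood level is the natural way to show that higher dose cohorts had higher exposure. As defined, the outcome would return about the same value whether participants absorbed a great deal of drug or took none.

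The blood markers have a related but lesser problem. They are meant to inform target engagement, yet their only defined time point is off drug. If felodipine lowered blood mHTT during treatment and the level recovered after stopping, the substudy's primary outcome could show nothing and be taken as absence of engagement. This carries weight for two reasons. CSF collection is optional, so blood will be the more complete source. The article also says, in its list of strengths and limitations, that engagement of autophagy in the brain cannot be measured directly.

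**Working it through.** **Inputs**

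- Terminal half-life: 25 h (Introduction).
- Time to steady state: 5 days (Introduction).
- Start of dosing: week 0 (Treatment allocation and dosing).
- End of dosing: week 58 (Overview; Table 1).
- Blood outcome time point: week 62 (Outcome measures).
- CSF outcome time point: week 57 (Outcome measures).

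**Consistency of the article's own figures.** 5 days = 120 h, and 120/25 = 4.8 half-lives. The fraction of steady state reached is 1 − 2^(−4.8) = 0.964. The stated 5 days therefore agrees with the stated 25 hours, and 62 − 58 = 4 weeks agrees with the stated washout.

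**Drug left at week 62**, assuming first-order elimination:

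- Washout = 28 × 24 = 672 h.
- Half-lives elapsed = 672/25 = 26.88.
- Residual fraction = 2^(−26.88) = 8.1e-9 of the level at stopping.

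**Sensitivity.** The half-lives other than 25 h, and the one-day visit shift, are assumptions.

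| Washout (days) | Half-life (h) | Half-lives elapsed | Residual fraction |
|---|---|---|---|
| 28 | 20 | 33.60 | 7.7e-11 |
| 28 | 25 | 26.88 | 8.1e-9 |
| 28 | 50 | 13.44 | 9.0e-5 |
| 27 | 25 | 25.92 | 1.6e-8 |
| 29 | 25 | 27.84 | 4.2e-9 |

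Even with the half-life doubled, 0.009% remains. At 25 h the level falls below 0.1% after log2(1000) × 25/24 = 10.4 days, well inside the washout.

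**Could the dose cohorts still be separated?** The cohort maxima run from 5 to 20 mg, a ratio of 4. If levels are proportional to dose (an assumption), that ratio is worth log2(4) = 2 half-lives out of 26.9. It cannot rescue a dose-exposure comparison at week 62.

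**Drug state at the other blood visits.** Eight-week spacing to week 40 gives weeks 8, 16, 24, 32 and 40. With week 57 that makes six draws during the treatment period. The last dose increase (cohort 3) is at week 6, so week 8 is 14 days later, beyond the stated 5 days to steady state. All six draws are therefore steady-state samples for participants still taking the drug.

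**Blood and CSF definitions side by side**

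| Analyte | Blood outcome | CSF outcome |
|---|---|---|
| Felodipine | week 62, off drug | week 57, on drug |
| mHTT | week 62, off drug | week 57, on drug |
| NfL | week 62, off drug | week 57, on drug |
| GFAP | week 62, off drug | week 57, on drug |

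The article gives no reason for the split.

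**The case against.** The strongest reply concerns the markers. Felodipine's half-life says how fast felodipine disappears. It does not say how fast mHTT, NfL or GFAP recover, and the article gives no recovery time for any of them. Fifty-eight weeks of exposure lie between the two samples. A reading after washout is a sensible way to ask whether an effect persists, which suits a drug proposed as disease-modifying. Week 62 is also the end point used for the clinical scales and MRI. This stands. A reader might infer that the blood mHTT outcome is as empty as the felodipine one, but the documents do not support that.

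A reader might also infer that blood and CSF cannot be related because they are taken in different drug states. They can be: blood is drawn at week 57 too, the same week as the CSF. Only the named outcome week differs. Nor do the documents give grounds here for moving the clinical scales.

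Two further replies carry less weight:

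- The Statistical methods wording, week 57 or 62, may permit a week 57 analysis. It most naturally reflects the mixture of CSF outcomes at 57 and blood outcomes at 62. It refers back to the outcome list without redefining it, and it speaks of exploratory endpoints, so it does not clearly reach the substudy's primary outcome.
- FELL-HD-s is a separate study whose full protocol is not shown, and it may specify on-treatment blood analyses. That would help, but the article states specific weeks. This is a stated definition that does not serve its purpose, not a detail left for later.

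**Conclusion.** For blood felodipine the outcome is wrong as written. Its expected value is about zero in every cohort (residual about 8e-9, and at most 9e-5 over the range tried), so it cannot show exposure or a dose-exposure relation. The conclusion rests on the article's half-life, on first-order elimination, and on the baseline blood being drawn before the first dose. That last point is inferred from treatment starting at week 0, since the article says so explicitly only for CSF. It would go too far to say that the planned paired t-test must be undefined: that needs every difference to be identical, and the handling of values below the assay limit is not given.

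For blood mHTT, NfL and GFAP the definition is a poor fit rather than an empty one. Week 62 can detect an effect that outlasts washout and may miss one that reverses. How much would be missed cannot be sized from the documents.

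Severity is moderate. The trial's primary outcome, adverse events attributable to felodipine, is unaffected, and the on-treatment samples are due to be collected in any case.

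**What to change.** 1. Replace the blood felodipine outcome with on-treatment concentration summarised by dose cohort, from the samples at weeks 8 to 40 and week 57. State the dose being taken at each sample, because the article allows participants to be moved to a lower dose or withdrawn from felodipine. A week 62 level may be kept as a check on washout.
2. Define the blood mHTT, NfL and GFAP contrasts as baseline to week 57, matching the CSF outcomes. Report week 62 as a separate, labelled post-washout contrast.
3. In Statistical methods, assign week 57 or week 62 to each endpoint by name.
4. State that baseline research blood is taken before the first dose.

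The cost is a wording change to the outcome definitions in FELL-HD-s and wherever they are repeated. No visit or sample is added. Aliquots are stored until the trial ends, so the change can be made and dated before any of them is analysed. That timing matters most for mHTT, because it is the substudy's primary outcome.
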